## Abstract

**Introduction:**

Chronic postsurgical pain (CPSP) is defined as pain that persists after a surgical procedure and has a significant impact on quality of life. Previous studies show the importance of psychological factors in CPSP, yet the majority of studies focused solely on negative emotions. This longitudinal observational study aims to broaden this knowledge base by examining the role of emotional state, emotion variability, emotion regulation and emotion differentiation on the child and the parent level for the development CPSP, and to describe pain and emotion-related trajectories following surgery.

**Methods and analysis:**

We intend to include 280 children and adolescents aged 8–18 years with a planned orthopaedic surgery and their parents. A total of five assessment time points is planned: 3 weeks before surgery (baseline), 2 weeks after surgery (post) and 3 months (follow-up (FU) 1), 6 months and 12 months after surgery. At baseline and post only, children and parents are asked to complete a daily diary thrice a day for a week where they rate their current emotional state and their pain severity (children only). Emotional state ratings will be used to calculate indices of emotion variability, emotion regulation and emotion differentiation. Children and parents will complete questionnaires at each time point, including measures on quality of life, social support, sleep, and symptoms of anxiety and depression.

To predict development of CPSP, generalised linear regression models will be used, resulting in ORs and 95% CIs. Pearson product-moment correlations between predictors and outcomes will be evaluated at each time point. The primary outcome of the prediction model is CPSP at FU1. For the trajectory analysis, the classification method K-means for longitudinal data will be used to determine clusters in the data.

**Ethics and dissemination:**

The Ethics Committee of the Canton of Zurich, Switzerland, has approved the study (ID: 2023-01475). Participants will be compensated, and a dissemination workshop will be held.

**Trial registration number:**

NCT05816174.

STRENGTHS AND LIMITATIONS OF THIS STUDYThis is a prospective, multicentre, longitudinal hospital-based study and the sample size allows to examine a range of risk and resilience factors.The longitudinal study design permits measurement of pain-related and emotion-related trajectories up until 12 months after surgery.The repeated assessments design will lead to an in-depth understanding of changes of risk and resilience factors over time.The primary limitation of this study is the potential loss to follow-up and missing datapoints due to several points of measurement.The results will be mainly based on self-reports, which are considered gold standard but can be subject to bias.

## Introduction

Chronic postsurgical pain (CPSP) is defined as chronic pain that persists over time (at least 3 months) following a surgical procedure and that has a significant impact on physical and psychosocial quality of life.^1 2^ Meta-analytical estimates in children and adolescents describe that around 25% of paediatric patients undergoing major surgery report chronic pain 3–12 months after surgery.^2^ Highest pain intensity ratings are observed in 2 weeks following surgery, with a steady decrease afterwards over the following 6 months,^3^ and pain ratings 2 weeks after surgery have been shown to predict the development of moderate to severe pain 1 year later.^4 5^ Further, most children and adolescents experience decreases in their physical activity levels following surgery, and it has been suggested that objectively monitored physical activity levels could be useful to indirectly assess functional recovery.^6^ A recent study in adolescents undergoing spinal fusion found that a majority of participants were characterised by a steep decrease of physical activity after surgery.^7^

Previous research has identified psychosocial risk factors that are associated with the development of CPSP, among them presurgical pain intensity, child anxiety, child pain coping efficacy, child sleep patterns and parental pain catastrophising.^2 8 9^ Generally, emotions and emotion-related factors are known to influence pain, pain-related disability and pain-related distress.^10 11^ There is some research on the role of emotion regulation in chronic pain,^12^ and the role of negative emotions is fairly well documented in the pain experience.^10 13 14^ However, other emotion-related factors such as emotion differentiation and emotion variability have yet to be studied in the context of paediatric CPSP, as they present as good targets for prevention and treatment modules and can be screened for in clinical practice.

### Emotion variability

Emotion variability describes the range of emotional fluctuations around an individual’s average emotional intensity.^15 16^ Greater emotion variability has been linked to more mental health symptoms in adolescents^17 18^ and higher emotion regulation demands.^19^ In paediatric chronic pain, one study found greater positive emotion variability to be associated with less pain-related interference and more engagement in activities despite pain.^16^ Emotion variability can be measured using the within-person SD of repeated assessments of current emotional state.^16 18 20 21^

### Emotion differentiation

Emotion differentiation defines the level of specificity people use when identifying their emotional experiences.^22–24^ Higher emotion differentiation indicates greater ability to differentiate between one’s own emotional states on a more fine-grained level and by using precise terms.^24^ High or low emotion differentiation can be calculated by means of intraclass correlations, where high consistency in emotion ratings across a predefined episode (eg, a week-long daily diary phase) suggests poorer differentiation.^24 25^ Previous research has demonstrated that higher emotion differentiation is associated with better mental health (see Seah and Coifman^26^ for a meta-analysis). To date, emotion differentiation has not been studied in the context of paediatric chronic pain.

### Emotion regulation

Emotion regulation refers to a person’s ability to influence what emotions they have, when they have them, and how they experience and express these emotions.^27 28^ A handful of previous studies has explored the role of emotion regulation in paediatric chronic pain^16 20 29 30^ yielding mixed results, while some found that different types of emotion regulation, namely expressive suppression and cognitive reappraisal, were associated with more frequent hospitalisation due to pain,^29^ and lower engagement in activities despite the pain,^16^ others did not identify significant associations between emotion regulation and pain intensity or pain-related disability.^20 30^ The habitual use of specific emotion regulation strategies is considered stable within individuals^31–33^ and can be measured by means of questionnaires.^19^

### Familial influences on paediatric pain

Previous research has shown that around 50% of children and adolescents with chronic pain have a parent who has had chronic pain in the past or is currently living with it.^34^ Parents and the family environment have been identified as a ‘key context’ (Simons *et al*
35 p. 702) regarding the understanding, assessment, and management of paediatric pain,^35^ and a bidirectional relationship between child functioning and parent factors is suggested.^35–37^ Regarding emotion-related factors, the family context is considered crucial: children learn the appropriateness of valence, duration and intensity of emotions and emotion expression by observing their parents and parents’ emotion regulation behaviours.^38 39^

In sum, previous studies have identified several risk factors for the development of CPSP, among them symptoms of anxiety, preoperative pain intensity and poorer sleep quality as well as parental catastrophising, even though the results were equivocal in part.^5 6 40^ The extent to which emotion-related factors can serve as resilience factors has had minimal investigation in the transition from acute to CPSP.^5^ Further, the promotion of resilience mechanisms as a prevention strategy has had limited focus in the context of paediatric chronic pain.^7 41^

### Objectives

The aim of this observational longitudinal study is to specifically examine the potential role of emotion-related factors (namely emotion variability, emotion differentiation and emotion regulation), as well as familial influences in the development of CPSP and describe pain-related and emotion-related trajectories following major surgery up to 12 months after surgery. We aim to identify whether and which emotion-related factors increase or decrease the risk for the development of CPSP after planned orthopaedic surgery. To the best of our knowledge, this is the first study to specifically examine these emotion-related factors as both potential risk and resilience factors in the development of CPSP.

## Methods and analysis

### Study design and setting

This is a prospective longitudinal observational study in patients undergoing scheduled orthopaedic surgery and their parents. The study starts in January 2024 and will continue to run through the end of January 2027. As scheduled orthopaedic surgeries are planned well in advance, patients can be approached early and asked about their interest in participating in the study. See figure 1 for an overview of assessment time points. The study is registered at ClinicalTrials.gov (NCT05816174). All participants will be recruited from three University Children’s Hospitals in Switzerland.

**Figure 1 F1:**
[figure not shown]
Overview of assessment time points. FU, follow-up.

### Patient and public involvement

Patients were not involved in the design of the study, however, the first 10 families that complete the postassessment will be interviewed and asked about their experience in the study so far. This feedback will be used to adapt study procedures if needed. The results will be disseminated to study participants via a newsletter and a dissemination event where participants, clinical collaborators and the interested public will be invited to discuss the study results.

### Sample and sample size calculation

The anticipated prevalence rate of CPSP is 25%, based on international estimates.^2 42^ The aim of this study is to recruit a sample of 280 child–parent dyads, resulting in an anticipated 70 children and adolescents with CPSP. In a power calculation for a logistic regression model with 10 events per variable (EPV)), this allows to examine 7 predictor variables with CPSP status as the primary outcome. Assumptions regarding EPV will be re-evaluated following recently proposed recommendations.^43 44^

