### Primary outcome

The primary endpoint is CPSP at FU 1. CPSP is defined as greater than minimal pain (pain intensity ≥3) on more than 50% of days as measured by daily diary over 7 days, and impairment in health-related quality of life (score of ≤74.9 on the PedsQL,^59^ ie, 1 SD below the population mean based on normative US data). The combination of pain and quality of life measures will result in a binary variable (CPSP yes/no). This measurement of CPSP is supported by previous research,^6 67 68^ and a modified definition of CPSP by the International Association for the Study of Pain.^69^

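### The 70 expected events and 7 predictors make no allowance for loss of the 3-month outcome, which the protocol itself names as its main limitation

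*Protocol article*

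**What the plan says.** Under Sample and sample size calculation, the protocol article states: "The anticipated prevalence rate of CPSP is 25%, based on international estimates". It then plans for "280 child–parent dyads, resulting in an anticipated 70 children and adolescents with CPSP" and concludes, at 10 EPV, that "this allows to examine 7 predictor variables with CPSP status as the primary outcome". No allowance for loss appears in that section. It adds that the EPV assumptions will be re-evaluated against newer recommendations.

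The strengths and limitations box says: "The primary limitation of this study is the potential loss to follow-up and missing datapoints due to several points of measurement".

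Statistical methods makes 10 EPV the rule that sets the number of independent variables, and also says that no selection will be made among the preselected predictors. Missing predictors and missing outcomes are to be handled by 100-fold multiple imputation.

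On the rate, the Introduction reports that "around 25% of paediatric patients undergoing major surgery report chronic pain 3–12 months after surgery". Under Primary outcome, a case at FU1 (3 months) needs "greater than minimal pain (pain intensity ≥3) on more than 50% of days as measured by daily diary over 7 days" together with a PedsQL score of 74.9 or lower.

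**The concern.** The event count is taken from the number recruited, not from the number expected to have the endpoint. The endpoint combines a seven-day pain diary with a quality-of-life questionnaire three months after surgery, so an incomplete diary or questionnaire may leave a child unclassified. A plan that calls missing data its main weakness should not rest on complete follow-up.

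The number of predictors follows directly from this count. The purpose of the regression is a risk score for CPSP, and a model with more terms than its events support is more prone to overfitting. Two statements in Statistical methods also pull apart if events fall short: the EPV rule calls for fewer terms, while the preselected predictors are not to be reduced. The article does not say which gives way.

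**Working it through.** **Inputs from the article:** 280 dyads recruited, anticipated prevalence 25%, 10 EPV (all under Sample and sample size calculation). **Assumed:** the proportion *d* of children without an FU1 outcome, because the documents give none. A range of 10 to 25% is shown.

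**Step 1: the article's own figure.** Events = 280 × 0.25 = 70. Predictors = 70 / 10 = 7. Both reproduce exactly, and only with *d* = 0. There is no slack, and 70 is itself only an expected value: with 280 observed outcomes and a true rate of 25%, the binomial probability of at least 70 events is 0.52.

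**Step 2: add loss.** Observed events = 280 × (1 − *d*) × 0.25. Terms allowed = events / 10, rounded down. EPV with 7 terms = events / 7.

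| Assumed loss | Observed events | Terms at 10 EPV | EPV if 7 terms are kept |
|---|---|---|---|
| 0% (as in the article) | 70 | 7 | 10.0 |
| 10% | 280 × 0.90 × 0.25 = 63 | 6 | 9.0 |
| 15% | 280 × 0.85 × 0.25 = 59.5 | 5 | 8.5 |
| 20% | 280 × 0.80 × 0.25 = 56 | 5 | 8.0 |
| 25% | 280 × 0.75 × 0.25 = 52.5 | 5 | 7.5 |

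Even 5% loss gives 280 × 0.95 × 0.25 = 66.5 events, hence 6 terms.

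**Step 3: do other provisions restore the 70?** Multiple imputation keeps all 280 children in the analysis and may recover some precision, but imputed outcomes are drawn from a model fitted to the observed data and are not further observed events. The planned re-evaluation concerns the EPV rule, that is, how many events each term needs. It does not concern how many events there will be.

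**Step 4: does the 25% match the endpoint?** The Introduction describes it as patients reporting chronic pain, 3 to 12 months after major surgery. The endpoint requires a pain criterion and a quality-of-life criterion, at 3 months, after planned in-patient orthopaedic surgery. Nothing in the article shows that the rate was estimated for, or adjusted to, that definition. The effect cannot be sized from the documents. Purely as illustration, a rate of 20% with no loss gives 280 × 0.20 = 56 events, and 15% gives 280 × 0.15 = 42.

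**The case against.** **Nothing is miscalculated.** This stands. The point is about an optimistic planning assumption, not an arithmetic error.

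**The plan adapts by itself.** If 10 EPV sets the number of variables, fewer events should mean fewer terms, and a detailed statistical analysis plan is promised before data export. This stands in part: the harm arises only if 7 terms are kept despite the shortfall. But the article publishes 70 and 7 as what the design delivers, and its rule against selection among the preselected predictors leaves open how the model would shrink.

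**The effect of loss is moderate.** This also stands. Over the assumed range, loss alone costs one or two terms under a rule of thumb that the authors already intend to revisit.

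**A stronger reading that a reader might infer** is that the 25% is a pain-only rate, so that the composite endpoint must be rarer and EPV must fall well below 10. The documents do not support this. The sample size section labels the 25% as the CPSP rate, the Introduction's definition of CPSP includes an impact on quality of life, and the cited sources are not at hand. An endpoint requiring both criteria cannot be more frequent than its own pain criterion, but the frequency of that criterion in this population is unknown, so the comparison says nothing certain about 25%. Timing could act in the opposite direction: the Introduction describes pain falling steadily over the six months after the early peak, so a 3-month rate could exceed one pooled over 3 to 12 months. The article gives no figure comparing orthopaedic with other surgery.

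**Conclusion.** The concern holds for attrition. The stated 70 events and 7 predictors require complete 3-month outcomes, contrary to the article's own main limitation. With 25% prevalence and an assumed loss of 10 to 25%, about 53 to 63 observed events are expected, which supports 5 or 6 terms, or an EPV of 7.5 to 9.0 if 7 are kept. The direction is certain for any loss, given the 25%; the size depends on a loss rate that the documents do not give.

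The match between the 25% and the endpoint is a fair caveat on definition and timing, without an established direction or size. The scenarios at 15 to 20% are illustrative and carry no weight in this conclusion. This is a sample-size assumption that should be corrected. It does not invalidate the design, the endpoint or the data collection.

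**What to change.** 1. Restate the planning figure as expected events with an observed FU1 outcome, giving the assumed loss. At 25% prevalence this is about 53 to 63 events and 5 or 6 terms for losses of 25% down to 10%.
2. Note that the 25% comes from a description that differs from the endpoint in definition and timing. If a scenario at 15 to 20% is shown, mark it as illustrative.
3. In the statistical analysis plan, fix the number of model terms from the observed, non-imputed FU1 event count before any predictor–outcome model is fitted.
4. Rank the preselected predictors in advance, so that any reduction follows a written order. This keeps to the intention of no data-driven selection and settles how the EPV rule and the no-selection rule work together.

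The cost is wording, plus one decision on ranking. No extra enrolment is needed. The downside is a less favourable stated number of predictors.

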### Eligibility criteria

We will include participants between 8 and 18 years who have a planned in-patient orthopaedic surgery at one of the study centres. The child–parent dyads must be able to read (for younger children: with help) and understand German. Exclusion criteria will be serious comorbid health condition (eg, cancer, severe neurological impairment, chronic illness requiring daily medication) and prior major surgery (eg, prior spine surgery). Mental health comorbidities are no reason for exclusion.

### Procedures

Potential participants will be informed about the study by the clinical collaborators at each study site during one of their presurgical visits (eg, anaesthesia preparation interview, scheduling visit). Based on the clinical routine of the study centres, the procedures might differ slightly. If patients fall within the required age range, the clinical collaborators will provide the family with a leaflet with the most important study information. On the leaflet, a QR-Code brings families directly to a site on the website of the University Children’s Hospital Zurich (main study centre), where they can find the most important information again. If families express their initial interest about the study, the physician will take a note and inform the study team, which will then contact the family. A member of the study team will then approach the respective family at their next visit at the hospital or via phone call and go through the informed consent/assent procedure with them. In all cases, parents sign the consent form for their own participation. In children under the age of 14 years, parents also sign the consent form for their child’s participation, while adolescents aged 14 years or more sign their own consent form. This is in line with the Human Research Act,^45^ which states that adolescents aged 14 years and more who are capable of judgement and who are to participate in a study with minimal risks can sign their own consent form. In participating hospitals, patients typically have (at least) two visits before the surgery. Once the written informed consent and assent is given, families will complete a battery of questionnaires as baseline measures before the surgery via direct link to the online questionnaires (see next section and table 1 for an overview; see online supplemental file 1 for an overview of reliability, validity, benefits and limitations of all questionnaires), using Research Electronic Data Capture (RedCap^46^). In addition, participants will be asked to download the smartphone application SEMA V.3,^47^ a free tool for ecological momentary assessment provided by the University of Melbourne, Australia, especially developed for research needs.

10.1136/bmjopen-2023-080174.supp1Supplementary data

**Table 1 T1:** Measures, tools, domain and time points for data collection

Domain		Measure	Completed by	BL	Post	FU 1	FU 2	FU 3
Demographics	Age, gender, school, school attendance and performance; family constellation, parental educational level and work status	Parent and self-report: online baseline questionnaire	Parent(s) and child	X				
Medical history	Neonatal intensive care (yes/no), previous surgeries (yes/no; which one), child’s pain history (pain duration, pain location)	Parent report: online baseline questionnaire	Parents	X				
	Complications in the hospital (yes/no) Pain treatment immediately following surgery	Child’s medication list in electronic health record	Data entered by study team		X			
Experience-sampling method	Positive and negative emotions (emotion variability and emotion differentiation)*	Items from the Positive and Negative Affect Schedule^48^	Daily diary: child and parent	X	X			
	Pain severity	Numeric Rating Scale (NRS), 0–10	Daily diary: child	X	X	X		
Psychosocial factors child								
	Pain severity (intensity, distress, interference^77^)*	Numeric Rating Scale (NRS), 0–10	Child self-report				X	X
	Preoperative screening	Paediatric Pain Screening Tool^51 52^	Child self-report	X				
	Functional disability	Functional Disability Index^54^	Child self-report	X	X	X	X	X
	Fear of pain	Fear of Pain Questionnaire^53^	Child self-report	X				
	Pain catastrophising	Pain Catastrophising Scale—three-item version^78^	Child self-report	X				
	Attachment; parent–child relationship	Security Scale^79^	Child self-report	X				
	Symptoms of anxiety and depression*	Revised Child Anxiety and Depression Scale-short version^56^	Child self-report	X	X	X	X	X
	Sleep	Pittsburgh Sleep Quality Index^57^	Child self-report	X	X	X	X	X
	Sensory processing sensitivity	Highly Sensitive Child Scale^58^	Child self-report	X				
	Emotion regulation*	Emotion Regulation Questionnaire—Child and Adolescent version^19^	Child self-report	X				
	Quality of life	Paediatric Quality of Life Inventory^59^	Child self-report	X	X	X	X	X
	Social support	Social Support Questionnaire for Children^60^	Child self-report	X				
	Post-traumatic stress symptoms	Child and Adolescent Trauma Screening^80^	Child self-report	X		X		
Psychosocial factors parents								
	Parents’ own pain history	2 questions: ‘(1) Have you ever and (2) are you currently living with persistent or recurrent pain for at least 3 months?’	Parent self-report	X				
	Postoperative pain measure (child’s pain)	Postoperative Pain Measure for Parents^62^	Parent report		X			
	Fear of pain	Parent Fear of Pain Questionnaire^35^	Parent self-report	X				
	Pain catastrophising	Pain Catastrophising Scale—three-item version^78^	Parent self-report	X				
	Anxiety and depression*	Anxiety and Depression Scale^63^	Parent self-report	X	X	X	X	X
	Sensory processing sensitivity	Highly Sensitive Person Scale^65^	Parent self-report	X				
	Emotion regulation*	Emotion Regulation Questionnaire^31^	Parent self-report	X				
	Quality of life	WHO Well-Being Index^66^	Parent self-report	X	X	X	X	X
Primary outcome								
Chronic postsurgical pain		Presence of CPSP: pain diary for seven consecutive days (NRS)+health-related quality of life (PedsQL, see above)				X		

*Primary predictors are marked with a *. Unmarked variables are considered secondary or exploratory.

BL, baseline; CPSP, chronic postsurgical pain; FU, follow-up; PedsQL, Paediatric Quality of Life Inventory.

Families will be called again 2 weeks after the surgery and asked to complete the postassessment via direct link to the questionnaires. Families will be contacted again 3 months (follow-up (FU) 1), 6 months (FU 2) and 12 months (FU 3) after surgery to complete the FU surveys and asked to complete the surveys at each assessment point within 1 week after receiving the link to the survey; up to 3-weekly reminders will be sent after the initial message.

In addition to the questionnaires at each assessment point, all participants (ie, children and parents) will complete daily diaries: To estimate the influence of emotion-related factors on pain trajectories, children and adolescents will complete two daily diary phases (ie, 2 weeks of daily diary) during which they rate both their pain severity and emotional state (referred to as ‘pain and emotions’ throughout the protocol; at baseline and postassessment), and one daily diary episode during which they only rate their pain intensity (referred to as ‘pain only’ throughout the protocol; at FU 1, see figure 1). Parents will complete two daily diary phases (at baseline and post) during which they exclusively rate their emotional state.

Daily diary—pain and emotions (two time points): At baseline and postassessment, children and adolescents will complete ratings of their pain severity on an 11-point Numeric Rating Scale with anchors 0=‘no pain’ and 10=‘worst pain possible’. Pain severity includes pain intensity, pain-related distress and pain-related interference; hence, participants will give three different ratings.^41 42^ The pain ratings will be used to classify the presence of acute postsurgical pain at the postassessment (in combination with a health-related quality of life rating; see overview of questionnaires for this time point in table 1). In addition, all participants will rate the extent to which they experience positive and negative emotions three times each day on their smartphone and during their normal daily routine over the course of 7 days. These ratings will be used to calculate a score of emotion differentiation (ie, the ability to differentiate between emotional states), a mean value of positive and negative emotions and an index of emotional variability^26 36 37^. The items of the short version of the Positive and Negative Affect Schedule for Children (PANAS-C) will be used to assess emotional state.^38–40^

Daily diary—pain only (once): To diagnose CPSP, participants will be asked to rate their daily pain severity for 7 days starting at FU1. Participants will be prompted at the end of each day to respond on an 11-point numeric rating scale with anchors 0=‘no pain’ and 10=‘worst pain possible’. In addition, daily medication use will be indicated (yes/no and listing medication in a free text field).

Number of steps taken each day will be counted as an indicator of changes in physical activity before and after surgery (ie, at the postassessment), measured by means of accelerometer (GENEActive, Activeinsights), an ambulatory, non-invasive activity-monitoring device that registers physical activity and can be worn around the wrist.

